**Method:**

For Phase I, a convenience sample of ~50 adolescents will be recruited. These participants will have their PAEE assessed in three different modes of commuting. Regarding phase II, a total of 300 adolescents from different schools in three Spanish cities will participate in this cluster randomized controlled trial. As many schools as necessary to meet the target sample will be included. In addition, each school will be randomized as either an intervention or control group. Participants from intervention schools will be asked to complete a school-based cycling intervention, while participants from control schools will be asked to continue their same habits for 8 weeks. The school-based cycling intervention will last for 8 weeks and will include *Bikeability* sessions, along with encouragement strategies to increase adherence to cycling to and from school.

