### Study population

2.2

In the Phase I of the ENERGYCO study, a convenience sample of 50 students (12–16 years old) will be recruited to assess the PAEE of different modes of commuting to school (i.e., walking, cycling, and motorized-vehicle). For Phase II, the ENERGYCO study will recruit a random sample of students (*n* = 300) from the three Spanish cities (i.e., Granada, Almería, and Jaén). The intervention aims to assess the effects of a school-based cycling intervention in the RMR and PAEE related to cycling to school, as well as its impact on others physiological, physical, emotional, and psychosocial outcomes in Spanish adolescents. The randomization process is presented in Figure 1.

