#### Study assessment protocol

2.6.1

In Phase I, participants will perform three different simulations (i.e., commute by motorized-vehicle, walking, and cycling [see Figure 2]): (1) a simulation of driving to school will be performed by motorized-vehicle. After all the calibration process of the Cosmed K5 (both, flow and gas analyzers will be calibrated before every gas exchange measurement), a face-mask attached to the K5 will be place and gas exchange will be check during a two-minute period before the measurement start. After the check phase, gas exchange recording start during a five-minute period, while participants remain seated. Then, the participants will simulate commute in a motorized-vehicle by remaining seated in a chair for another 15-minute period, having previously walked for 2 mins simulating that participants are moving toward the motorized-vehicle from home. After this first simulation, there will be a five-minute period of cooling down. The total time of this first test will be 27 min. (2) A simulation walking to school will be conducted in a closed circuit defined by the research staff. The same procedures mentioned before will be followed. Then, the participant will walk for 15 min (the participant will determine the speed and intensity of walking) and finish with a five-minute cool down; (3) Participants will simulate a cycling route. They will wait for five-minute after walking and they will start cycling during 15-minute period along the designated route. The simulation will finish with a five-minute cool down period. The total time used in the walking and cycling simulations will be 45 min. These times were chosen because an average walking speed of 4.4–4.6 km/h would not exceed the distance Spanish adolescents are willing to walk to their educational center (1,350 m) (52). While no study in Spanish adolescents indicates the distance, they are willing to cycle to school, we estimated a distance of 4,200 m, the threshold distance used for Australian adolescents (53), with which a speed of approximately 15 km/h would not exceed 15 min. Detailed visual information on the evaluation and calibration process of the Cosmed K5 (Cosmed, Rome, Italy) can be found at the following link.^1^ In order that one active mode of commuting (e.g., walking) does not affect the post exercise oxygen consumption, thus PAEE, of the subsequent active mode of commuting (e.g., cycling), participants will alternate randomly by first performing the simulation of walking or cycling. In addition, the alternation of starting on the bike and walking will be counterbalanced by having the same number of participants starting on the bike or walking. Finally, all data will be downloaded using PC OMNIA.9 software v3.30.79 (Cosmed, Rome, Italy).

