#### Statistical analysis

2.10.2

Descriptive analyses of all study variables presented with the mean (standard deviation) and frequencies (percentage) will be performed. Subsequently, the normality of the variables will be analyzed using histograms and normality tests. In Phase I, for the comparison of PAEE between the different modes of commuting (i.e., walking, cycling, and motorized-vehicle), a repeated measures ANOVA will be performed using the per-protocol approach. In addition, Student t-test or Mann–Whitney tests will be performed to compare the fluctuation of PAEE according to speed or distance commuted between active modes of commuting (i.e., walking vs. cycling).Within Phase II, the effects of the school-based cycling intervention on RMR and other health-related outcomes will be studied using an analysis of covariance (ANCOVA). Post-intervention RMR and other-health related values will be included as dependent variables, group (i.e., experimental group vs. control group) as fixed factor, and baseline outcome data as covariates. To evaluate the effect of the intervention on the secondary outcomes (i.e., physiological, physical, and psychosocial outcomes), we will conduct the same analysis used for the main outcomes (i.e., ANCOVA analysis using the intention-to-treat approach). Moreover, to control the variability between schools, the analyses will include adjustments for contextual and organizational variables, such as the SES of the school area, the length of cycling lanes, the availability of bicycle parking, and the level of engagement of teachers and students in the intervention. The estimates will be present as raw and standardized (z-scores; i.e., mean differences between follow-up and baseline data divided by the standard deviation), as an indication of the change the post-intervention z-scores will be calculated relative to the baseline mean and standard deviation. Effect sizes will be categorized as small (0.2 SDs), medium (0.5 SDs), and large (0.8 SDs), based on Cohen (93). Finally, to analyze the influence of covariates on the association between the intervention and the main outcomes (i.e., RMR and PAEE), mediation analyses will be performed. The intervention will be included as the independent variable, and the main outcomes as the dependent variables. Covariates included in the mediation analysis will encompass body composition, physical function, cognitive determinants, perceived barriers or autonomy, built-environment characteristics, weather, among others. In the statistical analysis, a value of *p* < 0.05 will be considered statistically significant.

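### The supplementary Phase I comparison of walking with cycling by speed or distance names tests for independent samples, although the same adolescents do both

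*Protocol article*

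**What the plan says.** Phase I is a within-person design. The abstract states "These participants will have their PAEE assessed in three different modes of commuting", and section 2.6.1 repeats it: "In Phase I, participants will perform three different simulations (i.e., commute by motorized-vehicle, walking, and cycling". The order of the two active modes is varied by design: "participants will alternate randomly by first performing the simulation of walking or cycling", with equal numbers starting on each. Section 2.2 gives the size: "a convenience sample of 50 students (12–16 years old) will be recruited to assess the PAEE of different modes of commuting to school".

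Section 2.10.2 then describes two Phase I analyses. For PAEE across the three modes, "a repeated measures ANOVA will be performed using the per-protocol approach". The second analysis is supplementary and names two options, Student's t and Mann–Whitney. It says that these "tests will be performed to compare the fluctuation of PAEE according to speed or distance commuted between active modes of commuting", which the text specifies as walking versus cycling. No paired version of either test is named. The significance threshold is p < 0.05.

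**The concern.** The two analyses in section 2.10.2 use the same participants, but only the first respects that each adolescent supplies a value in every mode. The second names Mann–Whitney, which assumes two independent groups and has no paired form; its paired counterpart is the Wilcoxon signed-rank test. Student's t-test can be paired or unpaired. As the parametric alternative to Mann–Whitney, it reads as the two-sample test.

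An analyst who followed the sentence literally would treat 50 walking values and 50 cycling values as coming from 100 different people. Differences between adolescents that affect both values, such as body size and fitness, would then stay in the error term instead of cancelling. At stake is precision in a sample that the Discussion already describes as relatively small and possibly short of power.

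**Working it through.** **Inputs from the protocol article.** About 50 participants in Phase I (section 2.2); each performs walking and cycling (abstract, section 2.6.1); threshold 0.05 (section 2.10.2). The article gives no sample-size or power figure for Phase I, so there is no stated figure to reproduce.

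**Assumptions, not in the article.** Two-sided testing; equal SD (sigma) in the two modes; within-person correlation rho of 0.3, 0.5 or 0.7; for power only, a mean difference of 0.4 SD.

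**Step 1: standard errors of the walking–cycling difference.**

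- Unpaired: sigma × sqrt(2/n) = sigma × sqrt(2/50) = 0.200 sigma.
- Paired: sigma × sqrt(2(1 − rho)/n).
- Ratio, unpaired to paired: 1/sqrt(1 − rho).

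| rho | Paired SE | Ratio |
|---|---|---|
| 0.3 | 0.200 × sqrt(0.7) = 0.167 sigma | 1.20 |
| 0.5 | 0.200 × sqrt(0.5) = 0.141 sigma | 1.41 |
| 0.7 | 0.200 × sqrt(0.3) = 0.110 sigma | 1.83 |

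At rho = 0 the ratio is 1 and nothing is lost.

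**Step 2: consequence for the test.** Simulation of 50 bivariate normal pairs, with 20,000 runs for the t-tests, 5,000 for Mann–Whitney and 2,000 for the signed-rank test:

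| rho | Type I error, unpaired t | Type I error, paired t | Power at 0.4 SD, unpaired t | Power, paired t | Power, Mann–Whitney | Power, signed-rank |
|---|---|---|---|---|---|---|
| 0.3 | 0.020 | 0.054 | 0.51 | 0.65 | 0.49 | 0.64 |
| 0.5 | 0.007 | 0.051 | 0.51 | 0.79 | 0.49 | 0.78 |
| 0.7 | 0.0003 | 0.048 | 0.52 | 0.95 | 0.49 | 0.93 |

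**Step 3: plausibility check.** A 0.4 SD difference divided by the unpaired SE is 0.4/0.200 = 2.0, close to the usual critical value of 1.96, so power near one half is expected whatever rho is. The paired quotients are 0.4/0.167 = 2.4, 0.4/0.141 = 2.8 and 0.4/0.110 = 3.6, which explains why paired power rises with rho.

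**What the simulation does not cover.** It tests a simple mean difference between modes. The affected analysis concerns how PAEE varies with speed or distance, and the article does not define that quantity further. The SE ratio applies to any pair of within-person values with equal SDs. The power figures are illustrative only.

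**The case against.** The strongest reply concerns scope. The main Phase I comparison, which includes walking and cycling, is by repeated measures ANOVA and keeps the pairing. The sentence at issue is an addition to it. That stands, and the point is confined to that addition. A reader might infer that Phase I as a whole discards the pairing; section 2.10.2 does not support this.

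Second, the t-test might be meant as paired, since a paired t-test is also a Student t-test and the sentence follows a repeated measures analysis. This is possible, so the error is certain only for the Mann–Whitney branch. The wording still needs correction, because on the paired reading the two alternatives in one sentence would assume different designs.

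Third, a reader might infer a risk of false positive findings. With positive correlation the opposite holds: the unpaired test rejects too seldom. Only a negative correlation would reverse this, and nothing in the article suggests one.

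Fourth, one might fault the plan for naming no order term. That does not stand as an error. Order is randomised and counterbalanced, which balances a simple order effect out of the mean difference, and a condensed article may leave such model detail to the full plan. Including order could recover some precision, but no figure for this can be derived from the article.

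Finally, section 2.7.1.2 links Phase I to Phase II through the predictive equations, not through this test, so the trial's intervention comparison does not depend on it.

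**Conclusion.** The point holds for the supplementary walking-versus-cycling comparison by speed or distance, and for nothing beyond it. The article describes paired data and names a test for independent samples. This contradicts the design and is more than a detail left open. Under positive within-person correlation the standard error is inflated by 1/sqrt(1 − rho), that is by 20% to 83% for rho between 0.3 and 0.7, and the test is conservative. The correlation and the 0.4 SD difference are both assumed, so the drop to about 51% power, from 65% to 95%, shows the possible order of the loss and is not an estimate of Phase I's power. The consequence is modest, but the correction is worth making because it is simple and the article itself is concerned about Phase I power.

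**What to change.** In section 2.10.2, replace the named tests for this comparison with the paired t-test or, if the within-person differences are clearly non-normal, the Wilcoxon signed-rank test. That is enough to remove the defect.

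An optional alternative is one linear mixed model for PAEE with mode, speed or distance (and its interaction with mode), walk-first or cycle-first order, and a random intercept for participant. It keeps the pairing and estimates directly how PAEE changes with speed or distance, for which a two-sample test has no term.

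Either change affects the analysis wording only. No additional participants, measurements or procedures are needed.

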#### School recruitment and randomization

2.4.1

In Phase I, a convenience sample of approximately 50 students will be recruited. A call to action will be used to engage adolescents through the development of infographics and information about the aims of this phase, which will be disseminated through social media, personal contacts, or emails. Since these tests will be conducted outside the school timetable, no schools will be directly contacted. Instead, parents or legal guardians will be responsible for contacting the research team if their children are interested in participating in the study and they provide their consent. In this call to action, incentives, such as activity wristbands will be given away to participating adolescents. For Phase II, a specific selection protocol will be implemented through a random draw. A list of all public secondary schools in each of the participating cities of the government educational institutions in Andalucía will be obtained. The schools in the three cities (Granada, Almería, Jaén) will be contacted by phone, and if they are interested in participating, they will have to meet a series of inclusion and exclusion criteria presented in Table 1. During the call, a meeting will be arranged with interested schools to explain to the management team and teaching staff the main objective of the study, as well as to obtain official consent to participate in the project from the school. After that, the research staff with the help of Physical Education teachers will recruit participants and their families, by visiting selected classes and explaining the study to prospective adolescent participants and finally requesting the family’s consent. The inclusion and exclusion criteria for the participants are presented in Table 2. To complete the sample of students in the intervention group, several schools may be needed, as not all students will be able to participate in the school-based cycling intervention due to family reasons, distance, predisposition, etc. To encourage as many students as possible from the intervention school to participate (with their families’ consent) in the school-based cycling intervention, an incentive system will be planned similar to other studies (42, 43). This incentive will consist of a voucher to be redeemed for sports equipment, provided that the participant has completed the 8 weeks of intervention and presents valid data at both baseline and follow-up. Once finished the baseline assessment, the participating schools will be randomly assigned through a draw to either a control or experimental group.

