##### Energy expenditure related to active commuting to school

2.7.1.2

PAEE related to different modes of commuting to school (i.e., walking, cycling, passive modes) will be measured using the Cosmed K5 portable metabolic system in Phase I. The Cosmed K5 has previously shown a good level of agreement compared to stationary metabolic carts at low cycling intensity (5.8% difference in VO_2_). At moderate intensities, it slightly underestimated VO_2_, VCO_2_, and energy expenditure (~6.6–6.9%). Additionally, during walking tests, the Cosmed K5 demonstrated high reproducibility, with a coefficient of variation of 4.5% for energy expenditure per kilometer and a concordance coefficient of 0.91. VO_2_ measurements were consistent, with low variability in the fraction of expired oxygen (coefficient of variation of 0.9%) (56). The Cosmed K5 is worn on the back with a harness and measures oxygen consumption (VO_2_) and carbon dioxide production (VCO_2_) in breath-by-breath mode. Before each assessment, the device will be calibrated using a reference gas mixture of 15.92% O_2_ and 5.03% CO_2_. Delay calibration for the breath-by-breath mode will also be performed (57). During the test, participants will breathe normally while commuting, and the Cosmed K5 will record data continuously. Data will be analyzed as the mean VO_2_ and VCO_2_ (ml/min) during each commuting mode. In Phase II, PAEE related to cycling will be estimated using predictive equations developed in Phase I. These equations will incorporate variables such as distance, speed, and heart rate, and will be cross-validated against PAEE measurements obtained with the Cosmed K5 to ensure accuracy. Therefore, data will be analyzed as the mean VO_2_ and VCO_2_ (ml/min) during each cycling trip to and from school, aggregated by participant during the intervention period.

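### The Phase I t-test or Mann–Whitney test meant to compare how PAEE varies with speed or distance has no speed or distance term, so with PAEE as defined it only compares the mode means

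*Protocol article*

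**What the plan says.** Section 2.10.2 gives two Phase I comparisons. For PAEE across the three modes, "a repeated measures ANOVA will be performed using the per-protocol approach". It then adds a Student t-test or Mann–Whitney test to "compare the fluctuation of PAEE according to speed or distance commuted between active modes of commuting". The article does not define *fluctuation*, and the sentence names no covariate, stratum, interaction, or outcome per kilometre or per unit of speed.

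Section 2.7.1.2 fixes the Phase I measure: "Data will be analyzed as the mean VO_2_ and VCO_2_ (ml/min) during each commuting mode". That is one value per participant and mode, on a per-minute scale.

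Section 2.6.1 has the same adolescents do both active bouts, and "participants will alternate randomly by first performing the simulation of walking or cycling". Each bout lasts 15 minutes. Walking speed is self-selected, with 4.4–4.6 km/h as the expected average. For cycling, the section assumes a distance "with which a speed of approximately 15 km/h would not exceed 15 min". Table 3 lists GPS distance, speed and duration as Phase I data.

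Section 2.7.1.2 also plans predictive equations from Phase I, with distance, speed and heart rate among their inputs, for use in Phase II.

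**The concern.** On its natural reading, the sentence asks how PAEE changes with speed or distance, and whether that relation differs between walking and cycling. This is a question about slopes. The two named tests compare one location between two sets of values, and nothing in them represents speed or distance.

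Two errors could follow. A significant result, which is likely if the modes simply differ in mean intensity, could be taken as a different dependence on speed. A real difference in slopes could go unseen. Mode and speed are also nearly inseparable in this design, so the mean contrast cannot be attributed to speed. Whether the tests are paired is a separate matter: a paired t-test has the same limitation.

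**Working it through.** **Inputs from the article.** About 50 adolescents (2.4.1), each walking and cycling for 15 min; expected speeds 4.4–4.6 and about 15 km/h (2.6.1); one ml/min mean per mode (2.7.1.2); significance at p < 0.05 (2.10.2; taken as two-sided). Phase I has no power figure to reproduce.

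**Step 1: speed, distance and mode.** Distance = speed × 0.25 h.
- Walking: 4.4 × 0.25 = 1.10 km to 4.6 × 0.25 = 1.15 km.
- Cycling: 15 × 0.25 = 3.75 km.

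With duration fixed, distance and speed carry the same information. The expected values for the two modes are far apart, so a mean difference between modes is a difference in mode, speed and distance together.

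**Step 2: what the test responds to.** Let PAEE in each mode be linear in speed: mean m plus slope b × (speed − average speed), plus a participant effect and residual error. The participant effect cancels in the within-person difference d (cycling minus walking), so
- E(d) = m_c − m_w
- Var(d) = b_w²·SD_w² + b_c²·SD_c² + 2·σ²

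Here SD_w and SD_c are the speed SDs and σ is the residual SD. The slopes do not enter the quantity being tested. They only add noise.

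**Step 3: illustration by simulation.** All values below are assumptions, with n = 50 within person. The slope test regresses d on both speeds and tests b_c = b_w.
- Set 1 (2,000 runs; ml/min): speed SD 0.6 walking, 2.0 cycling; participant SD 100; residual SD 80. Slopes 150 against 30 where they differ; means 900 against 1,300 where they differ.
- Set 2 (3,000 runs; arbitrary units): speed SD 0.5 and 1.5; participant and residual SD 0.5. Slopes 0.8 against 0.1 where they differ, otherwise 0.3; means 3.5 against 4.5 where they differ, otherwise 4.

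| Scenario | Set | Paired t | Mann–Whitney | Slope test |
|---|---|---|---|---|
| Slopes differ, means equal | 1 | 4.7% | not run | 97.4% |
| Slopes differ, means equal | 2 | 5.1% | 1.0% | 87.8% |
| Means differ, slopes equal | 1 | 100% | not run | 5.2% |
| Means differ, slopes equal | 2 | 100% | 100% | 5.4% |
| Both equal | 2 | 4.9% | 1.4% | 5.2% |

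**Step 4: why the slope-test power varies.** The large-sample SE of the slope difference is √2·σ/√50 × √(1/SD_w² + 1/SD_c²).
- Set 1: 1.414 × 80/7.071 = 16; 16 × √(2.778 + 0.25) = 27.8. The true difference of 120 is 4.3 SEs.
- Set 2: 1.414 × 0.5/7.071 = 0.1; 0.1 × √(4 + 0.444) = 0.211. The true difference of 0.7 is 3.3 SEs.

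The power figures therefore depend on the inputs, chiefly on how much walking speed varies. What the t-test detects does not depend on them.

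**Step 5: the per-kilometre reading.** If the outcome were PAEE per km, distance would enter through the outcome. In set 2 with equal means of 4 per minute, walking gives 4 × 15/1.125 = 53.3 per km (at 4.5 km/h) and cycling 4 × 15/3.75 = 16.0 per km. The ratio of 3.3 arises from speed alone. A paired t-test on this outcome rejected in 100% of runs in all three scenarios. It answers a narrower question, energy cost per km by mode, and does not compare slopes.

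**The case against.** The strongest defence is that *fluctuation* is undefined. PAEE according to speed or distance could mean PAEE per kilometre or per unit of speed. Section 2.7.1.2 itself cites energy expenditure per kilometre when it reports the device's reproducibility. A paired test on such an outcome would be coherent, and building derived variables is often left to an analysis plan. This stands in part: a reader might infer that the named tests cannot address the question under any reading, and the article does not support that. However, the only Phase I PAEE measure it defines is the ml/min mean, and the Mann–Whitney test treats the two modes as independent groups although the same adolescents do both. The sentence needs amending under either reading.

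A reader might also infer that the speed relation is left unanalysed, or that this test feeds the Phase II equation and weakens it. Neither follows. The predictive equations use speed and distance, and nothing in the article links this test to them. Equally, nothing says the equations test whether the relation differs between walking and cycling.

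The test is also not plainly redundant. The repeated measures ANOVA covers three modes, and no walking-versus-cycling contrast is stated. Finally, the simulations largely restate the logic of a test of means, and every input is assumed. That is correct, and they are offered only as illustration.

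**Conclusion.** The point holds in a limited form. With PAEE as section 2.7.1.2 defines it, the planned t-test or Mann–Whitney test does not match its stated question. It detects a difference in mode means and is blind to how PAEE varies with speed or distance, paired or not. This conclusion needs no assumed numbers beyond linearity within mode, used for illustration in step 2; the simulated rejection rates depend on their inputs.

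The consequence is confined to one additional Phase I analysis in about 50 volunteers. It does not bear on the randomised Phase II comparison, and the article gives no ground for saying that it affects the Phase II PAEE estimates. It is worth correcting before the Phase I data are analysed because the correction is cheap and the likely misreading is easy to foresee.

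**What to change.** Replace the t-test/Mann–Whitney sentence with a linear mixed model on the walking and cycling bouts: PAEE on mode, average GPS speed centred within mode, mode × speed and body mass, with a random participant intercept. Report the slope within each mode and the difference in slopes, with 95% confidence intervals. Use speed or distance, not both, since the 15-minute bouts make them equivalent.

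State two limits alongside it:
- No comparison of the modes at equal speed is made, because the expected speeds are far apart and it would require extrapolation.
- With one bout per mode, the slopes reflect differences in speed between adolescents. Fitness and body size may confound them, and adjusting for body mass deals with only part of this.

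If energy cost per kilometre was intended, define that as the outcome and compare the modes with a paired t-test or Wilcoxon signed-rank test.

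The cost is one sentence of analysis wording and the two caveats. The GPS, portable calorimetry and body-mass data are already planned in Phase I. The same rewording also settles the use of an independent-groups test on within-person data.
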